**Figure 1 Study Flow Diagram**

### Number of Participants

The study will aim to recruit 10 participants per study group (approximately 20 participants in total).

### Study Period/Duration of Participation

The study will involve:

- A treatment (six weeks) with follow-up for six weeks (fortnightly) and at six weeks following.

Total: approximately 18 weeks per participant.

The overall study period is expected to be September 2025 to August 2026.

### Recruitment of Participants

Participants will be recruited from the multidisciplinary foot clinics (MDF) and podiatry outpatient clinics at the RAH and TQEH. Patients in these services are well known to clinical staff and the investigators. Potential participants will be identified by clinical staff, and initial approach about participating in the trial will be performed by the patient's attending clinician (vascular, nursing, or podiatry). Information and consent will be provided by a clinical study investigator.

Participants will be given two weeks to consider participation, but will also be allowed to screen in earlier if they choose and are deemed by the investigator to have adequately considered their options. Participants will be specifically reminded during this process that participation or non-participation will not impact their care, and that they are allowed to withdraw from the study at any time.

### Inclusion Criteria

Prospective participants must meet all the following inclusion criteria to be eligible to participate in the study:

1. Adults at least 18 years of age.
2. Have a current diagnosis of diabetes mellitus (DM) characterized by at least one of the following:
  - currently under DM medication treatment

- with HbA1c > 6.5%
  - with fasting plasma glucose > 7.0 mmol/L
  - with plasma glucose > 11.1 mmol/L in the two-hour 75-gram oral glucose tolerance test (OGTT).
3. With at least one cutaneous ulcer on the foot, which meets all the following criteria:
- area between 2 and 20 cm^2 at the time of enrolment.
  - has been under the standard care of the Investigator for at least 4 weeks.

NOTE: if a participant has two or more ulcers that meet the inclusion criteria, only one ulcer will be selected as the study ulcer. The ulcer selected should be the one with the largest area. The other ulcers will be treated by standard care.

4. With ankle brachial index (ABI)  $\geq$  0.4 and/or toe pressure >30 mmHg on the limb with the study ulcer.
5. The participant has a life expectancy of at least 6 months as determined by the Investigator based on a combination of medical history, physical examination, vital signs, clinical laboratory tests, and other risk stratification assessments.
6. Able to follow the Investigator's instruction on ulcer care (in the opinion of the Investigator).
7. Able to provide written informed consent. If cognitive impairment is suspected but the patient otherwise meets criteria, consent will only be obtained with a friend or family member signing off as witness.

### **Exclusion Criteria**

If prospective participants meet any of the following exclusion criteria, they are ineligible to participate in the study:

1. Planned for revascularisation (open or endovascular) or any major or minor amputation of the index leg within the next 3 months.
2. Active moderate-to-severe infection in the study ulcer, or treatment with intravenous antibiotics within the past two weeks.
3. Any sign (clinical, radiographic) of osteomyelitis associated with the study ulcer.
4. Treatment with systemic immunosuppressants within 90 days of screening.
5. Active malignancy or history of malignancy within five years prior to screening (except for a past history of basal or squamous cell carcinomas).
6. Known history of HIV infection.
7. Received any investigational research agent within 60 days or within five half-lives of the last treatment (if the half-life of the investigational agent is known to be longer than 12 days) prior to the planned initiation of study treatment.
8. With any clinical condition or significant concurrent disease judged by the Investigator to complicate the evaluation of the trial treatment.

## **Method of Assigning Participants to Treatment Group**

Participants will be randomly assigned to one of two treatment groups once written informed consent has been obtained and eligibility established.

A participant identification (ID) number will be allocated to each participant who provides informed consent, so that participants can be identified without making assumptions about their subsequent eligibility for the study. Participants will be allocated to sequential, ascending 2-digit ID numbers (e.g, 01, 02, 03), which will provide a unique identifier. The participant will retain the same ID number for the duration of the study.

If a participant fails screening or discontinues from the study, the participant's ID number will not be reused.

Treatments will be prepared according to a list of study IDs and assignments created from random.org, with the spreadsheet of assignment retained by [name]. At no time will [name] have knowledge of patient identity or clinical information for any patient; and at no time will [name] or [name] know the assignment of a patient to PAW or control.

## **Withdrawal of Participants from Study**

Participants can terminate their study participation at any time and without giving a reason, without prejudice to further treatment. Participants who discontinue from the study will be asked about the reason(s) for their discontinuation only to determine the presence of any AEs. If possible and willing, they will be seen and assessed by an Investigator and have a final study visit. AEs should be followed up until resolved or stable and determined to be chronic.

Participants who withdraw from the study prior to the final scheduled visit will have the final visit procedures conducted at the time of withdrawal, if possible. If a participant withdraws due to the need for amputation of the foot/limb with the study ulcer, they will be asked to have the final visit procedures prior to the amputation, if possible.

If a participant withdraws due to the study wound being completely healed, they should have the final visit procedures.

On withdrawal, participants will have the opportunity to request that their existing data and samples be expunged from the study, to the extent it is possible to do so.

The Principal Investigator can exclude a participant from continuing in the study. Possible reasons for discontinuing a participant may include:

- Participant withdrawal of consent
- Inability to tolerate the study treatment
- Any unacceptable AEs, in the judgement of the Principal Investigator
- Participant's non-adherence to the protocol
- The use of another investigational research agent prior to Week 6 has been deemed necessary
- Termination of the study for administrative, financial, or other reasons.

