| To evaluate the efficacy of PAW, at 12 and 18 weeks after initiation of treatment | 
Efficacy analysis will be performed based on data collected up to 18 weeks after initiation of treatment. Assessment of efficacy will be based on the following outcome measures of the study ulcer:
 
 
• Days to complete ulcer healing
 
• Presence and severity of infection
 
• Changes in wound quality based on ulcer assessment
 
• Quality of Life (Cardiff Wound Impact Schedule)
 
 |

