### *Recording of Adverse Events*

All AEs that occur from the time of informed consent until the participant completes or withdraws from the study will be recorded in REDCap.

SAEs deemed possibly, probably or definitely related to study treatment occurring after the participant completes the study will also be reported to the Sponsor, or delegate, if the Investigator becomes aware of them.

It is preferable that AEs are reported as diagnoses if one is able to be made, rather than individual signs and symptoms. The AE description, onset and resolution dates, severity, causality and outcome must be recorded, as well as any actions taken.

Unless a diagnosis is made, or signs and symptoms are present, laboratory values or vital signs abnormalities should only be reported as AEs if they cause the participant to discontinue from the study, the Investigator feels it is clinically significant, or they meet a criterion for a SAE.

If an AE leads to premature discontinuation of the study, the appropriate pages of REDCap must be completed.

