#### *Follow-Up of Adverse Events and Serious Adverse Events*

All AEs and all SAEs must be followed by the Investigator until resolution, until the AE stabilises or is recognised as a permanent condition by the Investigator, or until the participant is lost to follow-up, whichever comes first. Follow-up investigations may be necessary according to the Investigator's medical judgement.

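### When a participant withdraws because amputation of the study limb is needed, recording of new adverse events can stop before the operation, so the amputation and later unrelated events may go unrecorded

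*Protocol*

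**What the plan says.** Four parts of the protocol bear on this.

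- **Section 3, Withdrawal of Participants from Study.** The text foresees this case: "If a participant withdraws due to the need for amputation of the foot/limb with the study ulcer", then "they will be asked to have the final visit procedures prior to the amputation, if possible". It also says of participants who discontinue that "AEs should be followed up until resolved or stable and determined to be chronic".
- **Section 5, Recording of Adverse Events.** The recording window is "All AEs that occur from the time of informed consent until the participant completes or withdraws from the study will be recorded in REDCap". The only later route is "SAEs deemed possibly, probably or definitely related to study treatment occurring after the participant completes the study will also be reported to the Sponsor", and it applies only if the Investigator learns of the event. For each recorded event, the outcome and the actions taken are required fields.
- **Section 5, Reporting and Follow-Up.** SAEs go to the Sponsor within 24 hours whatever their cause, with no end date stated. On follow-up: "All AEs and all SAEs must be followed by the Investigator until resolution, until the AE stabilises or is recognised as a permanent condition", or until loss to follow-up.
- **Table 1 (objectives) and Section 9.** The efficacy outcomes include "Days to complete ulcer healing", infection, wound quality and quality of life. Amputation is not named as an outcome. Section 9 summarises the reasons for early discontinuation and tabulates treatment-emergent events by system organ class and preferred term.

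**The concern.** Amputation of the study limb is among the worst courses a foot ulcer can take, and the Introduction itself names amputation as a severe consequence of infection. Under the definition in Section 5 it would ordinarily be serious, through permanent impairment of a body structure or hospitalisation.

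For a participant who withdraws for this reason, however, the last study visit is placed before the operation and the window for new events closes at withdrawal. Whether the operation is recorded then depends on how the preceding event was entered and followed, because no rule asks for the operation itself. The participants affected would be those doing badly, so any loss of data would be related to outcome.

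This is a first-in-human trial with safety as its primary objective and about 10 participants per arm. A single serious event is a large part of what it can show. No analysis plan can restore an event that was never collected.

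**Working it through.** The protocol states no amputation rate, sample-size calculation or target precision, so there is no figure of its own to reproduce. The check sets the rules side by side and then gives the scale.

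**1. Can an amputation occur during the trial?** The exclusion covers only amputations already planned within 3 months, about 91 days. Follow-up is 18 weeks: 18 × 7 = 126 days. Unplanned amputations are not excluded at any time, so the answer is yes.

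**2. What is recorded if the participant withdraws for this reason, has the final visit, and then has the operation?**

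| Item | Rule that applies | Captured? |
|---|---|---|
| Ulcer event that created the need, if recorded before withdrawal | Recording window; follow-up to resolution or stability; outcome and actions taken | Yes |
| Reason for leaving | Section 9 disposition summary | Yes, as a reason |
| The operation, as its own dated event | Falls after the window closes | Not required; may appear inside another event's record |
| New post-operative event judged unrelated | Outside the window; the later route needs a treatment relationship | No recording rule |
| New post-operative event judged related | The later route is worded for participants who complete the study | Unclear for a participant who withdrew |

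The 24-hour SAE rule has no end date and ignores causality. Read alone, it could reach the operation. Read with the recording window, it conflicts with it, and the protocol does not say which governs.

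**3. Size of one missed event.** Inputs: n = 10 per arm (Section 9, Sample Size Assumptions); x = 0 or 1 (assumed). Exact (Clopper-Pearson) 95% limits:

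- 0/10: lower 0; upper = 1 − 0.025^(1/10) = 0.308, so 0 to 30.8%.
- 1/10: lower = 1 − 0.975^(1/10) = 0.0025; upper solves (1 − p)^10 + 10p(1 − p)^9 = 0.025, giving p = 0.445. So 0.3 to 44.5%.

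The observed rate changes by 1/10 = 10 percentage points.

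**4. Chance that at least one amputation occurs among 20 participants**, 1 − (1 − p)^20, for assumed risks p over follow-up:

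| Assumed p | 2% | 5% | 10% | 15% |
|---|---|---|---|---|
| At least one of 20 | 33% | 64% | 88% | 96% |

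These are chances that an amputation happens, not that it goes unrecorded. The second depends on withdrawal and on how the preceding event was recorded, and the protocol gives no basis for a figure.

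**The case against.** The strongest case against is that the protocol already captures what matters. Deterioration that leads to amputation would normally begin before withdrawal, so it falls inside the window. It would then be followed to resolution or stability, with outcome and actions taken. If a non-serious event becomes serious, that must be reported within 24 hours, with no stated cut-off at withdrawal. A visit before the operation is reasonable, since the ulcer may not be assessable afterwards, and it documents an unhealed ulcer. The primary safety analysis runs only to 6 weeks, so a later amputation would not enter it.

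Much of this stands. It rules out the reading that the whole episode disappears. It does not close the gap:

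- Follow-up of an open event helps only if that event was recorded, and assessment at discontinuation depends on the participant being able and willing.
- A mention of surgery under outcome or actions taken is not a separately dated event in a table by preferred term.
- The discontinuation reason shows a need for amputation, not whether, when or at what level it was done.
- New unrelated events after withdrawal have no recording rule.
- Adverse events are to be recorded throughout participation, not only to Week 6.

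Two stronger readings are tempting and unsupported. A reader might infer that every participant who needs an amputation is withdrawn. The sentence is conditional, and amputation is not among the listed examples of reasons for the Principal Investigator to discontinue someone. A reader might also infer that days to healing will be summarised only over those who remain, which would flatter the arm with more amputations. No section says so, and missing-data procedures are left to the SAP.

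**Conclusion.** The concern holds in a limited form. The pre-operative final visit, the closing of the window at withdrawal and the narrow later route together allow a study-limb amputation, and new unrelated events after it, to go unrecorded as events. Loss is possible rather than certain, and it would be concentrated in participants with a bad outcome.

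One missed amputation would change an arm from 1/10 to 0/10, lowering the exact upper 95% limit from 44.5% to 30.8%. This assumes 10 participants in the arm, one amputation there, and no separate record of it. Whether amputations will occur, and how often one would be missed, cannot be derived from the protocol.

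The data-collection window is a protocol matter and should be settled before enrolment. How amputation enters the healing summary may properly sit in the SAP, so no bias in that summary is claimed here.

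**What to change.** Reconcile the section on withdrawal with the three Section 5 parts on recording, reporting and follow-up:

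1. Record amputation of the study foot or limb, with its date, as an SAE whenever it occurs up to Week 18, whatever its judged cause and whether or not study treatment has stopped.
2. Separate stopping study treatment from withdrawing consent to data collection. Unless that consent is withdrawn, continue collecting adverse events and vital and limb status to Week 18, by visit, telephone or records. The pre-operative visit can stay as the last assessment of the ulcer.
3. In the healing summary, count such a participant as not healed through Week 18. The details can go in the SAP.

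The end of follow-up needs one definition for this to work. The schedule of procedures gives the Week 18 visit as day 168, which is 168 / 7 = 24 weeks, and Section 6 refers to Week 24 assessments.

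The cost is a few sentences of protocol text, matching consent wording, and a record check for the few participants affected. A safety or healing figure may become slightly less favourable. No clinical management changes.

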## **Replacement of Participants**

Approximately 20 participants will be recruited in total. Additional participants may be enrolled into the study at the discretion of the Principal Investigator to ensure at least 10 evaluable participants per treatment group. Participants who withdraw due to adverse events (AEs) will not be replaced.

## **4 STUDY PROCEDURES**

### **Participant Information and Informed Consent**

The Investigator must provide adequate information regarding the study conduct and obtain written informed consent from the participant before any tests or investigations outlined in the study protocol are carried out.

The participant will be given time to read and understand the Participant Information and Consent Form (PICF), and have any questions answered. They may wish to take the PICF and consider it further, or to discuss it with their family before signing.

The PICF must be personally signed and dated by both the Investigator obtaining consent and the participant.

### **Overview of Study Visits**

Study procedures should be performed at relevant study visits in accordance with the schedule of procedures outlined in Table 1. The Principal Investigator or other study doctor will be present for study treatment at screening and at the week two visit at minimum to ensure patient safety and observe for AEs.

Participants will only be enrolled and randomised to study treatment if they meet all eligibility criteria, and none of the exclusion criteria.

Study visits will be arranged at Royal Adelaide Hospital and/or The Queen Elizabeth Hospital, aligning with patient clinical visit scheduling where possible to minimise inconvenience to participants. A window of plus or minus three days is permitted for Visits 1 to 6, and a window of plus or minus seven days is permitted for follow-up Visits 7-10. Study visits via home visit are permitted for Visits 3-10.

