**Risk/Benefit Assessment**

As a first-in-human trial, some unforeseen risks to participants are unavoidable; however, all existing preclinical data highlights minimal risk to human cells and wound healing. As a topical application, it is highly unlikely that any application of PAW can have systemic effects. No participant will have PAW applied until completion of an ongoing large-animal (pig) preclinical study demonstrates no ill effects.

As a novel agent applied to open wounds, it is possible that localised skin irritation may occur; the trial and care team will be aware of this as the most likely adverse reaction and tailor a care plan for cases where it eventuates in order to limit impact of irritation on the wound microenvironment and healing.

Preclinical mouse and pig models showed no signs of pain or discomfort on application of PAW, and our patients with DFU, who are predominantly neuropathic, have a decreased capacity to feel localised foot pain. If patients with incomplete loss of sensation do report any pain or discomfort from the rinse application, saline will immediately be applied to wash away PAW and the event reported as an adverse reaction.

As a Phase I study in patients without severe infection, benefits to participants are expected to be muted. We expect participants randomised to the experimental arm of this study to have reduced bacterial load and recurrent infection during study; preclinical data suggests that wound healing may also be improved for this group. Regardless, we expect participants in both groups to benefit from improved personalised care experienced by typical clinical trial participants.

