## **5 ADVERSE EVENTS**

Participants will be questioned and monitored throughout the study with regard to any adverse events (AEs) they may have experienced. An AE can therefore be any unfavourable and unintended sign (including an abnormal laboratory finding), symptom, or disease temporally associated with the use of a medicinal product, regardless of relationship to the medicinal (investigational) product.

Determinations of severity and causality of any AE can only be determined by a clinical Investigator without awareness of whether the treatment used is PAW or control.

An AE shall be classified as serious (a Serious Adverse Event, or SAE) if, in the opinion of either the Investigator or the Sponsor, it:

- Results in death.
- Is life-threatening, i.e., in which the participant was at risk of death at the time of the event.
- Results in permanent impairment of a body structure or body function
- Requires in-patient hospitalisation or prolongation of existing hospitalisation.
- Results in persistent or significant disability/incapacity.

Important medical events that are not immediately life-threatening and that do not result in death or hospitalisation may still be considered serious if, in the opinion of the Investigator, they jeopardise the participant or require intervention to prevent one of the other outcomes listed above. Such events should also be treated as SAEs.

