#### *Application of Treatment*

The treating clinician will identify the patient by their study ID and check that they have the appropriate ID-labelled treatment. All wound dressings should be removed, and if standard of care requires debridement of the wound, that debridement will be done prior to the application of study treatment.

A piece of sterile gauze is soaked in product, and applied to the wound for ten minutes. Other study or clinical procedures can be performed during the ten-minute period.

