#### *After the Application of Treatment*

Once dressing is applied, its application should be immediately removed if:

- in the opinion of the Investigator, a participant exhibits signs or symptoms of shock or an allergic reaction; OR
- in the opinion of the Investigator, a participant exhibits any other unacceptable AE that warrant its removal; OR
- if the participant requests its removal.

When a rinse dressing is removed, it should not be reapplied, and the time and date of removal should be recorded.

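### The doctor-attendance rule names screening, where no rinse is scheduled, so as written it does not require a doctor at the first application; the bedside removal rule also omits the pain trigger and saline wash-off promised elsewhere

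*Protocol*

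**What the plan says.** **Doctor attendance.** Protocol Section 4, Overview of Study Visits, states that the Principal Investigator or a substitute must attend: "other study doctor will be present for study treatment at screening and at the week two visit at minimum to ensure patient safety". No other sentence in the protocol requires a doctor to be present during an application.

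**When treatment is given.** The schedule of procedures, printed under Data collection in Section 4, has a Screening column separate from the treatment and evaluation visits. Its study-treatment row is blank at Screening and marked at Visits 1 to 6, with Visit 1 on Day 0. Section 3 on assigning participants adds: "Participants will be randomly assigned to one of two treatment groups once written informed consent has been obtained and eligibility established". The schedule repeats the eligibility review at Visit 1.

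**Reaction to the rinse.** The Risk/Benefit Assessment says that if a participant with some remaining sensation reports pain or discomfort from the rinse, "saline will immediately be applied to wash away PAW and the event reported as an adverse reaction". The rule used during application is in Section 7, After the Application of Treatment. It orders immediate removal in three cases. The first is "in the opinion of the Investigator, a participant exhibits signs or symptoms of shock or an allergic reaction; OR" The second is another unacceptable adverse event, again in the Investigator's opinion. The third is the participant's own request. On what follows removal it says only: "When a rinse dressing is removed, it should not be reapplied, and the time and date of removal should be recorded".

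**The concern.** The protocol describes the trial as first-in-human, with a product applied to open wounds. An unexpected local or allergic reaction is of most concern at the first exposure, and that is where a doctor's presence has most value. The one rule that secures a doctor is attached to a visit at which nothing is applied. Staff who follow the text would meet it with a doctor at screening and at week two, and none at the first rinse.

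The second matter is smaller. The saline wash-off is a protection that the protocol itself promises, yet it stands only in the background section on risk and benefit. A clinician working from the removal rule would take off the gauze and record the time. Taking off the gauze does not wash away liquid already on the wound.

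**Working it through.** There is no stated figure to reproduce. The check sets the passages side by side and counts.

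**1. Attendance rule against schedule**

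| Visit | Rinse scheduled? | Doctor required as written? |
|---|---|---|
| Screening | No | Yes |
| Visit 1 (Week 1, Day 0) | Yes, the first | No |
| Visit 2 (Week 2, Day 7) | Yes | Yes |
| Visits 3 to 6 | Yes | No |

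The rule and the treatment row meet at one visit only, week two. If week two is read as Day 14, the overlap moves to Visit 3, and Visit 1 remains uncovered.

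**2. Could screening and Visit 1 be the same day?** Nothing in the protocol says so. Randomisation waits for established eligibility. Blood is drawn at screening (Laboratory Tests), and inclusion criterion 5 draws on laboratory results. Eligibility is looked at again at Visit 1. These points suggest two occasions, but they do not rule out a combined day.

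**3. First applications covered**

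- Planned first applications: 10 per group × 2 groups = 20, of which 10 are PAW.
- Literal reading, separate days: 0 of 20 (0 of 10 PAW).
- Screening meant as Visit 1, or both on one day: 20 of 20.

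**4. Cost of covering them:** 20 applications × 10 minutes each = 200 minutes of doctor time in all.

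**5. Removal rule against the Risk/Benefit promise**

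| Element | Risk/Benefit Assessment | Section 7 removal rule |
|---|---|---|
| Reported pain or discomfort as a trigger | Yes | Named in 0 of 3 triggers |
| Saline wash | Yes, immediate | Not mentioned |
| Investigator's opinion needed | No | In 2 of 3 triggers |
| Gauze removed at once | Not stated | Yes |

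One case separates the two texts. A participant reports mild discomfort and does not ask for removal. The Risk/Benefit text calls for a wash. The removal rule calls for nothing unless the Investigator judges the event unacceptable.

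The wash is described as clearing away PAW, while Section 3 (Overall Study Design) blinds all clinical personnel. Staff cannot know which liquid is on the wound, so the instruction works only if it applies to both arms.

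**The case against.** The best case against the first part is that it is a slip that any reader would correct. The sentence speaks of presence for study treatment, none is given at Screening, and so it makes sense only for the first application. Other features reduce the practical risk. The attendance rule sets a floor. Home visits are allowed only from Visit 3, so the first rinse takes place at a hospital. A clinical Investigator assesses the ulcer at every visit, and contact dermatitis is looked for at every visit. All of this is accurate, and it is why the 0 of 20 is a statement about the literal text and not a forecast. None of it requires a doctor at Visit 1, however: the clinical Investigator who assesses the ulcer is not stated to be one.

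Against the second part, the Risk/Benefit text is already binding and the removal rule does not contradict it. Blinded staff would in practice wash any wound that hurts. That stands: this is an omission from the section used at the bedside, and a matter of alignment.

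Two stronger readings are tempting and are not supported.

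- **That the person applying the rinse is not told to act at once.** Section 7 does give the handling to the treating clinician ("The treating clinician will identify the patient by their study ID and check that they have the appropriate ID-labelled treatment") and ties two triggers to the Investigator's opinion. But the rule itself demands immediate removal, a participant's request needs nobody's opinion, and the saline step in the Risk/Benefit text needs none either. Nor does anything prevent the treating clinician from being an Investigator.
- **That pain reports enter the primary safety measure as adverse reactions without a causality assessment.** The Risk/Benefit wording could suggest this, more so because, where the wound needs debriding, "that debridement will be done prior to the application of study treatment", which offers another cause of pain. But Section 5 says that "causality of any AE can only be determined by a clinical Investigator without awareness of whether the treatment used is PAW or control", and it requires the Investigator to assess causality for every adverse event and to have it recorded. The Risk/Benefit wording does not override that.

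**Conclusion.** The attendance rule is wrong as written and should be corrected. Literally it secures a doctor at 0 of 20 first applications; on the reading most likely intended, at 20 of 20. The 0 rests on screening and Visit 1 being separate days, which the schedule suggests and no passage settles. The documents do not support the inference that the sponsor plans to give first doses without a doctor, or to treat before randomisation. The finding is that the written rule does not secure what it was evidently written to secure.

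The removal rule lacks a trigger and an action that the protocol promises elsewhere. This is secondary. The number of participants affected cannot be estimated from the protocol and is probably small, because it expects most participants to be neuropathic.

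Both points concern clinical conduct, so a statistical analysis plan would not be the place to settle them.

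**What to change.** 1. **Overview of Study Visits:** replace 'at screening' with 'at Visit 1 (first application)' and keep the week two visit. The cost is at most about 20 attendances of ten minutes, and nothing if attendance at Visit 1 was already intended.
2. **After the Application of Treatment:** add as a trigger 'if the participant reports pain or discomfort from the rinse'. Then add: 'On removal for any of these reasons, rinse the wound at once with sterile saline, in both arms.' Leave the judgement of other unacceptable adverse events with the Investigator, and keep the existing rules on reapplication and recording.

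The second change goes slightly beyond the present promise, since the wash would follow every kind of removal and not only pain. Its downside is that a few rinses may be stopped earlier than under the current list. Both changes are best made before the first application or, if treatment has begun, by prompt amendment.
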